**Intestinal inflammation**

Intestinal inflammation status will be monitored in a non-invasive manner.

At each scheduled time point, one stool sample will be collected and frozen at -20°C for fecal calprotectin analysis. Fecal calprotectin levels will be measured, using a standardized technique, in each participating center.

Fecal calprotectin concentration will be evaluated using the ELISA method (Calprest Eurospital, SpA, Trieste, Italy). Briefly, 0.1 g of feces are suspended in a buffer, pre-diluted, homogenized and centrifuged. The supernatant is collected and analyzed by an ELISA (according to the manufacturer’s instructions) with a specific polyclonal antibody. The reference values of fecal calprotectin range between 0 and 50 micrograms/g, values between 50 and 100 micrograms/g are considered intermediate, and require follow-up, whereas values over 100 micrograms/g indicate intestinal inflammation.

**Sample Collection and Handling for FISH evaluation**

FISH was performed on fecal samples collected from 22 CF children in stable clinical conditions, 20 age-matched healthy controls. Stools from 10 CF children on antibiotic treatment were also collected and analysed. CF children, in stable conditions, were then treated with LGG (6x109 cfu/die) or placebo for 4 weeks and intestinal microbiota was evaluated again immediately after their administration.. Based on the results obtained by DGGE and RT-PCR, we chose to investigate the presence of *Bacteroides* and *Eubacterium rectale* since both species were consistently reduced in CF children.

*F. prausnitzii* was chosen because it has been associated with the pathogenesis of inflammatory bowel diseases.

Fecal samples, fixed in Carnoy's solution and embedded in paraffin, were cut longitudinally into 4-μm sections, placed on SuperFrost slides (Thermo Scientific, Italy) and incubated with hybridization solution (20 mM Tris–HCl, 0.9 M NaCl, 0.1% SDS and 1% formamide, pH 7.4) with EUB mix positive control oligonucleotide probes (100 ng of EUB I, EUBII and EUBIII). For *Bacteroides*, *E.rectale* and *F. prausnitzii* the slides were incubated with hybridization buffer with 25 ng of their respective FISH probes for 45 min at 50 °C and evaluated by Nikon 80i Eclipse epifluorescence microscope. Using a Nikon DS-U2 color camera and NIS-Elements imaging software (Nikon, Tokyo, Japan). Bacteria were quantified by count within a 10×10–μm area of the microscopic field representative of the region of interest. The oligonucleotide probes used in this study were synthesized by MWG Eurofins (MWG Operon Ebersberg, Germany). All samples were analyzed with the Eub338 mix probe conjugated with fluorescein isothiocyanate (FITC, green signal) at the 5′-end (positive control, which is specific for all bacteria), and an appropriate species-specific probe was conjugated with a single fluorescent carbocyanine (Cy3, red signal) molecule.

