***Endpoints***

Primary endpoints:

- Modification of intestinal inflammation
- Modification of intestinal microflora composition

***Methods*** .

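### The microflora primary endpoint is a count per 10×10 µm area, with no fixed number or placement of areas and no stated all-bacteria denominator

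*Protocol*

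**What the plan says.** The protocol's Endpoints section lists "Modification of intestinal microflora composition" as one of two primary endpoints. How it is measured is set out only under Sample Collection and Handling for FISH evaluation. Fecal material is "cut longitudinally into 4-μm sections", hybridised with probes for *Bacteroides*, *E. rectale* and *F. prausnitzii*, and then: "Bacteria were quantified by count within a 10×10–μm area of the microscopic field representative of the region of interest".

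The same section says that all samples were also analysed with the Eub338 mix in a green label, described as "positive control, which is specific for all bacteria", and that "an appropriate species-specific probe was conjugated with a single fluorescent carbocyanine (Cy3, red signal) molecule". The two signals can therefore be told apart. The only role given to the all-bacteria signal is that of positive control.

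The section does not say how many areas are counted, how they are placed, whether the reader works on coded slides, or whether target counts are related to the total. The paragraph on microflora under Statistical Analysis of Secondary Endpoints adds a descriptive analysis with t and Mann-Whitney tests, and no normalisation.

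**The concern.** Composition is a share: how much of the bacterial population belongs to a given group. A count per fixed area is a density. Followed as written, the rule would record a change in all three target groups whenever a stool section is looser or denser, even if the mix of bacteria had not moved.

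Two further features are left open. The area has to be representative, but nothing says how that is decided. And an area of 100 µm² may contain few bacteria of any one group, in which case chance alone moves the count considerably.

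At stake is the interpretation of a primary endpoint. In Aim 1, CF stool is compared with healthy stool without randomisation, so a difference in stool density between the groups could be reported as a difference in microflora. In Aim 2, LGG against placebo, noise from density, area choice and counting makes a real effect harder to see.

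The protocol itself fixes this laboratory rule, so it is not a detail left to a separate analysis plan.

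**Working it through.** **The plan's own figure.** No sample size is given for microflora. The only one stated, 35 per group, is for intestinal inflammation (0.90 vs 0.63, one-sided 0.025, power 0.80). It can be reproduced: the unpooled two-proportion formula without a correlation factor gives 34.8, and the log-odds formula gives 43.6 × (1 + 0.6)/2 = 34.9. It carries no information about the precision of the bacterial count.

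**Density against composition (no assumption about counts needed).** Expected target count = D × A × p, where D is bacteria per µm², A = 100 µm² and p is the target's share. If D halves and p stays the same, the target count halves. The total count is D × A, so target/total = p whatever D is. For illustration, 4 targets among 40 bacteria become 2 among 20: the count falls by 50% and the share stays at 10%.

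**Inputs for precision**
- Area: 10 × 10 = 100 µm²; with 4 µm sections, 400 µm³ (FISH section).
- Children: "FISH was performed on fecal samples collected from 22 CF children in stable clinical conditions". This is about 11 per arm if split equally; the split is an assumption.
- Mean target count per area, m: not in the protocol; assumed 2 to 30.
- True between-child CV, c: not in the protocol; assumed 0.3, 0.5 and 1.0.
- Number of areas, k: not in the protocol; one and ten are compared.
- Counts are taken as Poisson and areas as independent. Correlation between areas would make the gain from ten areas smaller than shown.

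**Counting CV = 1/√(k·m)**

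| m | one area | ten areas |
| --- | --- | --- |
| 2 | 71% | 22% |
| 5 | 45% | 14% |
| 10 | 32% | 10% |
| 20 | 22% | 7% |
| 30 | 18% | 6% |

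**Share of between-child variance due to counting, one area = 1/(1 + m·c²)**

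| m | c = 0.3 | c = 0.5 | c = 1.0 |
| --- | --- | --- | --- |
| 5 | 69% | 44% | 17% |
| 20 | 36% | 17% | 5% |

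Counting makes up more than half of the variance only if m < 1/c², that is, below about 11, 4 and 1.

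**Power for a 50% relative difference, two-sided 5%** = Φ(0.5/(s·√(2/n)) − 1.96), with s = √(c² + 1/(k·m)). Worked case n = 11, m = 5, c = 0.5:
- One area: s = √(0.25 + 0.20) = 0.671, power 42%.
- Ten areas: s = √(0.25 + 0.02) = 0.520, power 62%.

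| n per arm, m | c = 0.3 | c = 0.5 | c = 1.0 |
| --- | --- | --- | --- |
| 11, m = 5 | 59% → 94% | 42% → 62% | 19% → 21% |
| 11, m = 20 | 88% → 97% | 57% → 64% | 21% → 21% |
| 35, m = 5 | 97% → 100% | 88% → 98% | 48% → 54% |

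Each cell shows one area → ten areas.

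**What the denominator does and does not do.** The CV of a share is √((1 − p)/(p·N)), with N the total bacteria counted. For p = 0.10 and N = 30 it is 55%, against 1/√3 = 58% for the raw count of 3. With ten areas (N = 300) it is 17%. The ratio removes the density effect; only more areas reduce the counting noise.

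**The case against.** Several stronger readings are tempting, and the text does not carry them.

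- *Counting noise dominates the endpoint.* The protocol gives no count, density or between-child variance. Dominance holds only at low counts or a small true spread; at a between-child CV of 1.0, biological variation dominates over the whole assumed range. This objection stands.
- *A single area, picked by eye.* The wording is singular, but 10×10 µm could be the counting unit, repeated over several fields. A camera and imaging software are named, and nothing says who or what selects the area. What can be said is that number and selection are unspecified.
- *The denominator is on every slide and unused.* The text says all samples, not every slide; two-colour labelling makes the same slide likely. Calling Eub338 a positive control does not prove that its counts were never used as a denominator. What can be said is that no normalisation is stated.
- *The treatment comparison is biased.* The trial is randomised and double-blind. If the slide reader is also masked, which is not stated, area choice adds variance rather than bias between arms. Density biases that comparison only if it differs by arm, and nothing in the protocol suggests so.

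Two other points have weight. A ratio is not neutral: if treatment changed the total bacterial load, the ratio could hide or mimic a change in one group. That is a reason to keep the absolute count, but not to let it stand for composition. Also, the FISH section is written in the past tense and mixes several sets of samples. It nevertheless covers the children given LGG or placebo for four weeks, and it is the only FISH method given.

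**Conclusion.** The point holds as a measurement rule that is badly fixed and cheap to improve. The mismatch between a count per area and an endpoint named composition needs no assumption about counts: as written, the rule cannot separate a change in bacterial mix from a change in stool density. This matters most for Aim 1, where groups are not randomised; in the LGG-placebo comparison the main effect is avoidable variance.

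The loss of precision is unknown. The range runs from material (power 42% instead of 62% at c = 0.5, m = 5) to negligible (19% instead of 21% at c = 1.0). Those figures rest on assumed counts, assumed between-child spread, Poisson counting, about 11 children per arm and a contrast of one area with ten. They show what could be at stake, not what has been lost.

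**What to change.** Replace the counting sentence in the FISH section with a rule along these lines: *On coded slides, target (Cy3) and total (Eub338, FITC) bacteria are counted in the same areas. A fixed number of 10×10 µm areas (for example 10 to 20) is placed by a systematic random rule. The composition endpoint for Aims 1 and 2 is the pooled ratio of target to Eub338 counts; the absolute count per area is reported alongside.*

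Both parts are needed: the ratio deals with density, and the number and placement of areas deal with precision and selection. The absolute count is kept because the ratio alone would not show a change in total bacterial load.

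The cost is reading time. With three target groups and two colours, 10 to 20 areas mean 10 × 3 × 2 = 60 to 20 × 3 × 2 = 120 counts per sample, against 6 with one area. Samples, probes, microscope and software stay the same, provided both signals can be read on the same slide. The protocol does not describe reader capacity, so the workload should be checked before the number of areas is set. Slides already read would need a recount.

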***Ethical aspects***

The study will be conducted in accordance with Good Clinical Practice (GCP). Patients will be informed about the purpose of the research, the nature of the research, responsibilities, the scientific use of the data, the right of withdrawal. They will be instructed to continue taking all currently prescribed medication and treatments, and to phone or e-mail immediately if any adverse event occurs. The investigators will evaluate the patients for any possible adverse event at each visit, using standard clinical criteria. During clinical visits patients will be segregated according to bacterial status. Clinical researchers will phone patients weekly to monitor side effects and to encourage compliance.

Written informed consent to participate to the study will be provided by the parents or legal guardian of each participant. All enrolled patients must have consented to their medical records being viewed by authorized personnel and by regulatory authorities. The protocol has been submitted and approved by the Ethics Committee of University of Naples Federico II (Coordinating Center) (protocol number 0939; approved on April 22nd, 2009). Potential risks for study subjects will be monitored and only for clinically relevant events, by which the patients can modify their life style changes, subjects should drop out of the study.

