Our hypotheses are supported by preliminary data from our centre. In a subsequent study, the incidence of intestinal inflammation was investigated in a population of 30 CF children, otherwise unselected [6]. Fecal calprotectin and rectal nitric oxide concentration in rectal dialysis bags were used as non invasive markers of intestinal inflammation [6]. It was observed that intestinal inflammation was very frequent in CF. Mean calprotectin values were 4 times above normal in CF children. Nitric oxide rectal production was also increased, which supports the concept that the distal intestine represents a target organ in CF disease. In a trial with the probiotic strain *Lactobacillus rhamnosus* GG (LGG) in children with CF colonized with *Pseudomonas aeruginosa,* calprotectin and nitric oxide concentrations were decreased and values of these inflammatory marker did not return to fully normal values [6].

In a subsequent prospective, randomized, placebo-controlled, cross-over study, we investigated the incidence of pulmonary exacerbations and hospital admissions in CF children colonized with *Pseudomonas aeruginosa* [7]. Pulmonary exacerbations and of hospital admissions were fewer in patients receiving the probiotic LGG than in patients treated with oral rehydration solution (ORS). Probiotics administration also resulted in a slight increase in forced expiratory volume in 1 sec (FEV1). These data suggest that probiotics may delay respiratory impairment in CF children and support a relationship between intestinal and pulmonary inflammation.

Although the evidence available is largely preliminary and should be regarded with caution, our data implicate colonic intestinal microflora in the pathogenesis of CF, as follows:

- Colonic intestinal microflora is changed in CF as a result of changes in intestinal environmental and aggressive therapy.
- Mild to moderate intestinal inflammation is frequent in CF, at least in part, as a consequence of abnormal microflora composition.
- Administration of selected probiotics reduces intestinal inflammation and also exerts beneficial effect on intestinal microbiota .

The intestine, and specifically the intestinal microflora, may therefore be an important target for treatment in CF. The administration of probiotics is a promising treatment approach for children who are on heavy load of antibiotics.

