***Study design***

Study activities are reported in the timeline (Table 1).

| **Parameters** | **Visit 1a** | **Visit 2b** |
| --- | --- | --- |
| Written informed consent | x |  |
| Randomization |  | x |
| Clinical examination | x | x |
| Genetic analysis (if not already performed) | x |  |
| Demographic | x |  |
| Anthropometric | x | x |
| Intestinal inflammation | x | x |
| Microflora |  | x |
|  |  |  |

Study design

Patients meeting the inclusion criteria will be enrolled and randomly assigned to the treatment or placebo group arm. Patients randomized to the treatment arm will receive 6x109 CFU of LGG once a day for a 1-month period. Patients randomized to the placebo group will receive placebo once a day for 1 months. LGG and placebo formulations will be masked and coded appropriately to ensure blindness. LGG formulations will be composed of maltodextrin (163 mg), gelatine capsule (75 mg), LGG (60 mg), magnesium stearate (2 mg). The placebo composition will be maltodextrin (223 mg), gelatine capsule (75 mg) and magnesium stearate (2 mg). LGG and placebo capsules will be identical in appearance, taste and color and only a numeric code will differentiate the two formulations.

For these patients systemic inflammation and intestinal microflora using Fluorescent in situ Hybridization will be evaluated before starting treatment and at the end of it (0 and 1 month

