***Specific statistical analysis***

# *Statistical Analysis for primary endpoints*

**INTESTINAL INFLAMMATION:** The binary outcome variable is the presence of at least one intestinal inflammation episode for subject j in cluster i (i=1,..,N, j=1,…n). Based on the results of Bruzzese et al[6], a proportion of subjects with at least 1 episode of intestinal inflammation of 0.90 is expected; a reduction of 30% of such proportion is considered clinically relevant (0.90 vs 0.63). These values determine an odd of experiencing at least one intestinal inflammation episode 0.19 times smaller in the treatment group than in the control group. A intra-cluster correlation coefficient () between the two time occasions of 0.6 is assumed (this is rather a cautionary value because a smaller coefficient is expected) With a one-sided  of 0.025 and a statistical power (1-β) of 0.80, 35 subjects per treatment group are needed to detect such difference in favour of the LGG compared to placebo after twelve months. Alternatively, by using the sample size obtained for powering the analysis of pulmonary exacerbations, all other things being equals, a power of 92% will be reached.

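### The protocol has children leave the study after undefined clinical events, which loses their only post-baseline outcome for reasons that may depend on arm and inflammation.

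*Protocol*

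**What the plan says.** Protocol, Ethical aspects: after a general statement that risks will be monitored, "only for clinically relevant events, by which the patients can modify their life style changes, subjects should drop out of the study". The events are not defined. The consequence is leaving the study, and no other section says what happens to follow-up when only the capsules are stopped. The same section provides regular contact: "Clinical researchers will phone patients weekly to monitor side effects and to encourage compliance".

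Protocol, Study design: the laboratory assessments "will be evaluated before starting treatment and at the end of it (0 and 1 month". Protocol, Intestinal inflammation: "At each scheduled time point, one stool sample will be collected and frozen at -20°C for fecal calprotectin analysis". No sample at withdrawal and no follow-up after an event is described.

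Protocol, Endpoints: one of the two primary endpoints is "Modification of intestinal inflammation"; the other is change in microflora composition. Both need the 1-month stool.

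Protocol, Statistical Analysis for primary endpoints: "a reduction of 30% of such proportion is considered clinically relevant (0.90 vs 0.63"; the odds in the LGG group are put at "0.19 times smaller in the treatment group than in the control group". With one-sided alpha 0.025, power 0.80 and a correlation of 0.6 between the two occasions, 35 subjects per group are required. No allowance for dropout is mentioned.

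Protocol, Significance, on an earlier cross-over study in children colonized with *Pseudomonas aeruginosa*: "Pulmonary exacerbations and of hospital admissions were fewer in patients receiving the probiotic LGG than in patients treated with oral rehydration solution (ORS".

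**The concern.** Each child has one post-baseline measurement. A rule that sends a child out of the study before it is taken removes that child from both primary endpoints, and no later analysis can recover a stool that was never collected. The trigger is an event during treatment, so randomization does not protect against imbalance in who is lost. If the events are linked both to the assigned product and to intestinal inflammation, the children who remain are no longer comparable between arms. If they are not so linked, the cost is precision only, in a sample calculated without a margin for loss.

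**Working it through.** **Inputs.** From the protocol: 0.90 (placebo) and 0.63 (LGG) inflamed, correlation 0.6, one-sided alpha 0.025, power 0.80, 35 per group. Loss rates are assumptions, because the protocol gives none.

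**1. Reproduce the protocol's figures.**
- Odds ratio = (0.63/0.37)/(0.90/0.10) = 0.189, stated as 0.19.
- n = (1.960 + 0.842)² × [1/(0.90×0.10) + 1/(0.63×0.37)] / (ln 0.189)² = 7.849 × 15.401 / 2.772 = 43.6.
- Two-occasion factor (1 + 0.6)/2 = 0.8, so 43.6 × 0.8 = 34.9, or 35 per group.

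The stated 35 is therefore reached with no inflation for dropout.

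**2. Power after loss, same formula.** Power = Φ(1.665 / √(15.401 × 0.8 / n) − 1.960).

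| Loss per group (assumed) | n remaining | Power | n to recruit to keep 35 |
|---|---|---|---|
| 0% | 35 | 80% | 35 |
| 5% | 33.25 | 78% | 37 |
| 10% | 31.5 | 76% | 39 |
| 20% | 28 | 71% | 44 |

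The last column is 35/(1 − loss), rounded up.

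As a second view, exact power for a plain comparison of 0.90 with 0.63 at two-sided 0.05, going from 35 to 30 per arm, falls from 78% to 72% with the chi-square test and from 70% to 61% with Fisher's exact test. The loss of five per arm costs about 6 and 9 percentage points respectively.

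**3. Bias if only children with a 1-month stool are compared.** Suppose a fraction d of inflamed children leaves and no non-inflamed child does. The observed proportion is p(1 − d)/[p(1 − d) + (1 − p)], so observed OR = true OR × (1 − d on LGG)/(1 − d on placebo).

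| Inflamed children lost, placebo / LGG (assumed) | Observed placebo vs LGG | Risk difference (true 0.27) | OR (true 0.189) | OR if truth is 0.90 in both arms |
|---|---|---|---|---|
| 20% / 10% | 0.878 vs 0.605 | 0.27 | 0.213 | 1.125 |
| 30% / 10% | 0.863 vs 0.605 | 0.26 | 0.243 | 1.29 |
| 10% / 20% | 0.890 vs 0.577 | 0.31 | 0.168 | 0.89 |
| 20% / 20% | 0.878 vs 0.577 | 0.30 | 0.189 | 1.00 |

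If loss is unrelated to inflammation within each arm, the observed proportions stay at 0.90 and 0.63 and there is no bias, even when the arms lose different numbers.

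**4. Direction.** The earlier cross-over result suggests that more events could occur on the comparator, which corresponds to the first two rows and works against LGG. Side effects of the product could cause more loss on LGG, which corresponds to the third row and flatters LGG. Nothing in the protocol decides between them.

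**The case against.** The sentence is a restriction, since it permits dropout only for certain events and a further clause about life style narrows it. Treatment lasts one month. The children are stable at entry, with no hospitalization, regimen change or oral or parenteral antibiotics in the preceding two weeks. Losses may be few. This stands, and it limits the likely size. It does not change what happens to the outcome when the rule applies.

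A reader might infer that the children removed are the sicker ones, that they come mainly from placebo, and that a benefit of LGG is hidden. The protocol does not support that chain. The events are undefined, and the surrounding text concerns adverse events and side effects as much as illness. The cross-over study had a selected population and a different comparator, and no calprotectin results are given for children who had events. Direction must be left open.

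The analysis set and the handling of missing data may be in an analysis plan that is not shown, so it cannot be said that the protocol prescribes a completers' analysis. Section 3 of the working shows only what such an analysis would do. The point that survives is narrower: a stool that was not collected is beyond the reach of any analysis plan.

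The sample size section also offers an alternative, the number planned for pulmonary exacerbations, with 92% power. That number is not given, so the margin it would provide cannot be checked.

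Finally, measuring on treatment is defensible in a one-month pilot. That is an argument about which effect to estimate. Collecting the stool and recording when capsules stopped keeps both options open.

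**Conclusion.** The concern holds in a limited form. As written, the rule turns an undefined clinical event into the loss of both primary outcomes, and the protocol describes nothing to prevent this. The cause arises after randomization, so bias is possible in either direction. Under the assumed loss patterns with a true odds ratio of 0.189, the observed value ranges from 0.168 to 0.243. With no true effect it ranges from 0.89 to 1.29. These figures assume that only inflamed children leave and that only children with a 1-month stool are compared; actual event rates may be much lower.

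The effect on power is modest. At up to 20% loss it falls from 80% to about 71% by the formula behind the 35. It would be wrong to set the 61% for Fisher's test against the protocol's 80%, because Fisher's test starts at 70% with 35 per arm; most of the remaining gap comes from the choice of test and formula. The change is worth making because it is cheap and must be made before samples are missed.

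**What to change.** Leave the clinical decision on the capsules as it stands. Replace the instruction to leave the study with wording that a child who has such an event remains in follow-up unless consent is withdrawn, is asked for the 1-month stool, and is analysed in the randomized arm. Record the event, the date capsules stopped and any antibiotics, so that a sensitivity analysis can be shown.

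The cost is a short change to the protocol text and one stool sample from families who are already phoned weekly. The downside is that some outcomes will be measured partly off treatment, which may dilute an on-treatment effect; the recorded dates allow this to be examined. If some loss is still expected, state the assumed rate and raise the recruitment target accordingly, for example from 35 to 39 per group at 10%.
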